myofascial (PMMF) flap a practical alternative for large oral cavity defects [18]. One major drawback 
of the PMMC flap is its bulk, which is influenced by the subcutaneous fat overlying the muscle and can hinder speech and swallowing 
rehabilitation, especially in anterior oral cavity and pharyngeal sites. This issue is more problematic in female or broad-chested patients 
and complications may be worsened when the mandible is preserved. Other limitations include intraoral hair growth, chest wall deformities 
and technical challenges with pedicle rotation. The PMMF flap, consisting of the pectoralis muscle and fascia without a skin island, addresses 
many of these drawbacks and has been reported as a versatile reconstructive option, although it remains underrepresented in the literature 
[19]. Partial hypopharyngeal defects following total laryngectomy (TLE) also pose reconstructive 
challenges. Loss of speech, impaired swallowing and complications such as fistulas, especially in previously irradiated patients, demand 
tailored approaches to optimize outcomes. While many techniques use free or regional flaps to create a cutaneous lining, the PMMC flap has 
lost favor because of its bulk and poor pliability. To overcome these issues, Robertson and Robinson introduced the PMMF flap in the 1980s, 
reducing complications. However, comparative evidence between PMMC and PMMF flaps remains limited [20]. 
Our study evaluates the post-operative outcomes of both flaps in tongue reconstruction. Most reconstructive techniques involve inverting a 
myocutaneous or fasciocutaneous free flap onto the remaining pharyngeal mucosa, forming a cutaneous lining. Historically, the pectoralis 
major myocutaneous (PMMC) flap has been widely used, but its bulkiness, poor pliability and risk of complications have reduced its 
popularity. To address these issues, Robertson and Robinson proposed the pectoralis major myofascial (PMMF) flap in the 1980s, which 
eliminates the skin island and reduces complications. Despite promising results, comparative studies between PMMC and PMMF flaps remain 
limited [20]. Therefore, this study aims to compare and evaluate the functional and aesthetic 
outcomes of the Pectoralis Major Myocutaneous (PMMC) flap versus the Pectoralis Major Myofascial (PMMF) flap for Type III and Type IV 
tongue defect reconstruction in patients operated on for squamous cell carcinoma of the tongue. Oral squamous cell carcinoma (OSCC) 

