## Materials and Methods:

The study will be a parallel group randomized trial. It will be conducting from February 2025 to September 2026. This clinical study will 
take place at the Department of Oral and Maxillofacial Surgery, Siddharth Gupta Memorial Cancer Hospital, Sawing, Wardha. The research will 
be carried out under the auspices of the Datta Meghe Institute of Higher Education and Research, Sawing, Wardha Institutional Ethics 
Committee (IEC) approval from Datta Meghe Institute of Higher Education and Research (DMIHER) (DU) has been obtained and the process will 
begin after explaining the detailed treatment protocol to the patients. A total of 24 patients will be assessed for biopsy-proven cases of 
SCC, with 12 patients meeting the criteria for the study.

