## Sample size calculation:

The sample size was calculated using Cochran's formula Considering a Z value of 1.96, a prevalence (P) of total flap necrosis reported 
as 2% (0.02) and a desired margin of error (e) of 8% (0.08), the formula was applied as:

n=z^2^(pq)/e^2^

n = 1.962 *0.02*(1-0.02)/0.08*0.08

= 11.76

Thus, a minimum of 12 patients were required for the study in each group (Total=12x2=24). The prevalence data were obtained from the 
study conducted by Milenovic *et al.* [22]. After diagnosis, patients will be divided 
into two groups by computer generated randomization and then alternatively select for the reconstruction with pectoralis major myocutaneous 
flap or pectoralis major myofascial flap.

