## Inclusion criteria:

[1] All the patients age 18 years and above with Biopsy proven case of Squamous Cell Carcinoma of Tongue

[2] Type III and Type IV Tongue defects according to Ansari classification

[3] Patients fit to undergo surgery ASAI

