## Study procedure:

Procedure will be done at Siddharth Gupta Memorial Cancer Hospital (SGMCH), DMIHER, Sawangi, Wardha for patients presenting with non-
healing ulcers over the tongue.

[1] Patient Evaluation: Patients reporting to the Department of Oral and Maxillofacial Surgery will undergo a thorough examination.

[2] Case History: A detailed medical, dental and personal history will be documented.

[3] Clinical Examination: A comprehensive assessment of the oral cavity, focusing on the non-healing ulcer sites, will be conducted.

[4] Biopsy: A biopsy will be performed for histopathological examination to confirm the presence of squamous cell carcinoma.

[5] Radiographic Examination: Patients with confirmed squamous cell carcinoma will undergo a MRI to assess the extent of the lesion and 
detect any lymph node metastasis

This protocol ensures accurate diagnosis and appropriate management for patients presenting with suspected tongue cancer at SGMCH. After 
diagnosis, patients will be divided into two groups by computer generated randomization and undergo surgery under all aseptic protocols. 
After surgery, the patient will be monitored and after 1 week, 3 months and 6 months, they will be evaluated for functional and aesthetic 
outcomes, according to which the PMMC and PMMF flap will be judged. The two groups will be divided based on the type of reconstruction to 
be done after wide local excision or composite resection of the lesion and suitable neck dissection, which are 1) Group I - Reconstruction 
of surgical defect in squamous cell carcinoma of tongue with pectoralis major myocutaneous flap 2) Group II- Reconstruction of surgical 
defect in squamous cell carcinoma of tongue with pectoralis major myofascial flap. Once a pre-surgical workup has been completed, which 
includes pre-anaesthetic fitness, signed, showed and fully stated consents. After this pre-operative photos will be taken and the surgery 
will be performed. The conical assessment of the outcomes of the two types of reconstruction held would be done on the basis of the functional 
and aesthetic outcomes of the procedures post-operatively after 7 days, 1 month and 3 months of follow-up, which would help in keeping a 
close eye on the progress of the patients.

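### The sample-size section adds an alternate-selection step to computer randomisation; the rest of the article describes randomisation alone, and the two must be reconciled

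*Protocol article*

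**What the plan says.** The protocol article describes allocation in several places.

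- **Abstract and Materials and Methods:** the abstract speaks of random allocation to two groups. Materials and Methods states: "The study will be a parallel group randomized trial".
- **Sample size calculation:** after diagnosis, patients are divided "into two groups by computer generated randomization and then alternatively select for the reconstruction with pectoralis major myocutaneous" flap or the myofascial flap. This is the only place where a selection step follows the randomisation.
- **Study procedure:** after "diagnosis, patients will be divided into two groups by computer generated randomization and undergo surgery under all aseptic protocols". No alternation is mentioned, and Groups I and II are defined by the flap used.

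On eligibility, the second inclusion criterion is "Type III and Type IV Tongue defects according to Ansari classification". Study procedure lists biopsy and MRI of lesion extent before the allocation sentence, and places reconstruction after excision or composite resection. The third exclusion criterion removes small lesions suited to primary closure.

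On the difference between the flaps, the Background says that the bulk of the myocutaneous flap can hinder speech and swallowing rehabilitation, and adds: "This issue is more problematic in female or broad-chested patients".

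**The concern.** Random allocation and alternation are different methods, and only one of them can decide the flap. Read literally, the sample-size section has two steps, and the second assigns the flap. Under alternation the order is fixed. The operating team necessarily knows which flap it used last, so it would know the next one before deciding whether and when to enrol a patient.

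The article itself supplies a motive to act on that knowledge. It describes the myocutaneous flap as less suitable in women and broad-chested patients, and under Expected outcome it asks whether the myofascial flap is superior. Speech and swallowing are secondary outcomes, so steering by sex or build would bear directly on what is compared. The tests listed under Statistical analysis cannot repair such selection afterwards.

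The secondary concern is order. A patient is allocated before resection, but the eligibility criterion is worded as a defect, which resection creates. As written, a patient could be randomised and then fail an inclusion criterion, which invites exclusion after allocation.

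**Working it through.** **1. Number of patients.** Inputs from Sample size calculation: z = 1.96, p = 0.02, e = 0.08.

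n = z² × p × (1 − p) / e² = 3.8416 × 0.02 × 0.98 / 0.0064 = 11.765

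This reproduces the stated 11.76, rounded up to 12 per group and 24 in total. The figure is not disputed here; it only sets the 24 used below.

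**2. Predictability if alternation is used.** After the first assignment, the other 23 are determined: 23/24 = 95.8%. If the first is a fair guess, the expected share guessed correctly is (0.5 + 23)/24 = 97.9%. Only 2 sequences are possible.

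**3. Predictability under random methods.** In each case the guesser knows all past assignments and names the likelier arm.

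- Simple randomisation: 50%.
- One random list forced to 12:12, with C(24,12) = 2,704,156 possible sequences. Expected correct guesses = 12 + ½ × (2²⁴ / C(24,12) − 1) = 12 + ½ × (16,777,216 / 2,704,156 − 1) = 12 + ½ × 5.204 = 14.60. As a share, 14.60/24 = 60.8%.

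Alternation is therefore close to fully predictable, against 50% to 61% for a single random list.

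**4. What steering could do (assumption, not from the article).** Suppose k of the 12 patients in each arm are there by steering, and that those steered to one arm differ in prognosis by 1 SD from those steered to the other. Each arm mean moves by k/12 SD in opposite directions relative to an unsteered allocation, so the bias is 2k/12 SD:

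| k per arm | Bias |
|---|---|
| 1 | 0.17 SD |
| 2 | 0.33 SD |
| 3 | 0.50 SD |

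The article gives no information on k or on the prognostic difference, so this shows scale only.

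**5. Timing against eligibility.** The order in Study procedure is: work-up including MRI, allocation, surgery, reconstruction. The criterion names a defect, not an anticipated defect. One patient lost after allocation is 1/12 = 8.3% of an arm. The article gives no rate at which the actual defect differs from the expected one. If that rate were 10%, 20% or 30% and such patients were excluded, 24 allocated patients would leave 24 × 0.9 = 21.6, 24 × 0.8 = 19.2 or 24 × 0.7 = 16.8.

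**The case against.** The strongest reply is that *alternatively* is loose English for one or the other. The word is followed by two flaps joined by *or*. The abstract, Materials and Methods and Study procedure all describe random allocation, and because the groups are defined by flap, nothing remains for alternation to decide once the group is drawn. The English is loose elsewhere too. This reply has weight: a reader might infer that the trial certainly allocates by alternation, and the documents do not support that. It does not remove the point. The sentence describes a further selection after randomisation, nothing in the article rules out the literal reading, and site staff could follow it.

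It may also be said that concealment and block details belong in a fuller document. That is right, and their absence is not the complaint. The complaint is a stated step that conflicts with the other sections.

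On timing, a reader might infer that allocation happens at the moment of diagnosis and that the defect type can be known only after resection. The text says after diagnosis, with MRI beforehand and small lesions screened out. The classification's rules are not in the document, so whether the type can be assigned from the planned resection cannot be checked. Randomising on anticipated extent is a legitimate design. What stands is that the criterion does not say this is what is meant.

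**Conclusion.** The point holds as a contradiction in the stated allocation method. One section adds a selection step that the others do not have. On one reading the assignments are predictable (23 of 24); on the other the sentence misdescribes a randomised trial. Both readings require a change to the text. The predictability figure and the bias illustration apply only if alternation is actually used, which the document does not settle, and the bias sizes also rest on the stated assumptions about steering.

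The timing issue is secondary: a mismatch between how eligibility is worded and when allocation happens, not proof that patients will be wrongly randomised. A reader might go further and infer that the trial needs stratification by defect type with varying block sizes. The article gives no Type III to Type IV mix on which to judge that, and in 24 patients incomplete blocks could upset the 12:12 balance, so it is not part of this point.

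**What to change.** 1. In Sample size calculation, delete the clause that introduces alternate selection. There and in Study procedure, state that a single computer-generated random list, concealed until the patient is enrolled, alone decides the flap.
2. The stated study period is February 2025 to September 2026, so check how any patients already enrolled were allocated. If alternation was used for any of them, report it.
3. Resolve the timing in one of two ways. Either word the second inclusion criterion as the anticipated Type III or IV defect, judged from examination and MRI, and analyse all randomised patients in their allocated group; or allocate once the defect has been classified after resection.

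The cost is mainly wording. Someone has to prepare and hold the list, preferably outside the operating team. Under the first timing option, some analysed patients may turn out to have another defect type. Under the second, the flap is known only during the operation, so planning and consent must cover both. The sample size and the two reconstructions stay as they are.

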## Inclusion criteria:

[1] All the patients age 18 years and above with Biopsy proven case of Squamous Cell Carcinoma of Tongue

[2] Type III and Type IV Tongue defects according to Ansari classification

[3] Patients fit to undergo surgery ASAI

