## Abstract

Reconstruction following extensive resection of tongue squamous cell carcinoma remains challenging because the optimal pedicled flap for 
achieving superior functional recovery and aesthetic outcomes is still uncertain. Therefore, it is of interest to compare pectoralis major 
myocutaneous (PMMC) and pectoralis major myofascial (PMMF) flaps for reconstruction of Type III and Type IV tongue defects in patients 
undergoing surgical treatment for squamous cell carcinoma. Twenty-four eligible patients will be randomly allocated into two groups, and 
post-operative outcomes including flap-related complications, tongue shape, swallowing, speech and tongue mobility will be evaluated at 1 
week, 1 month and 3 months using standardized clinical assessment scales. Functional and aesthetic outcomes between the two reconstruction 
techniques will be analyzed using appropriate statistical methods to determine differences in clinical performance and patient rehabilitation. 
Thus, data shows to generate evidence that supports selection of the most effective pedicled flap for tongue reconstruction and improves 
functional recovery, quality of life and clinical decision-making in resource-constrained settings.

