## Statistical analysis:

Following data collection, data will be entered into Microsoft excel worksheet (Microsoft, USA). Data analysis will done using IBM 
Statistical Package for Social Sciences (Statistics for Windows, Version 21.0. Armonk, NY: IBM Corp.) Categorical data will be described in 
terms of frequencies and percentages. Continuous data will be presented by mean and standard deviation (SD). Comparison of means to assess 
functional and aesthetic outcomes in reconstruction of Type III and Type IV Tongue defects with Pectoralis Major Myocutaneous Flap VS 
Pectoralis Major Myofascial Flap in patients being operated for squamous cell carcinoma of tongue will be done using Repeated Measures 
ANOVA and unpaired 't' test. For categorical data, chi square test will be used to compare the proportions. For analysis, p-value less than 
0.05 will be considered statistically significant.

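### Type III and Type IV defects are pooled, and the named comparison of the shape and function scores takes no account of defect type; adjusting for the type planned before surgery would be a cheap gain

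*Protocol article*

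**What the plan says.** The Inclusion criteria section admits two defect classes: "Type III and Type IV Tongue defects according to" a named classification. The Abstract states that "Twenty-four eligible patients will be randomly allocated into two groups", and the Sample size calculation section gives "a minimum of 12 patients were required for the study in each group (Total=12x2=24".

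Allocation is described in two places. The Sample size calculation section divides patients "into two groups by computer generated randomization and then alternatively select for the reconstruction". The Study procedure section repeats the computer-generated division, places it after diagnosis and before surgery, and requires an MRI beforehand to show the extent of the lesion. Neither place names a stratum.

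The Statistical analysis section names both defect types in the sentence that sets the comparison of means, and then treats them as one population. The methods are repeated measures "ANOVA and unpaired 't' test. For categorical data, chi square test will be used to compare the proportions". No defect-type factor or covariate is mentioned.

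Tongue shape, swallowing, speech and mobility are secondary outcomes, each scored 1 to 5 (Tables 1 to 4). The primary outcomes are complications.

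**The concern.** Scores for tongue shape and function after resection may well depend on the extent of the defect as well as on the flap. Table 1 ends at a small rounded remnant, Table 4 grades protrusion and lateral movement, and the Background ties the choice of reconstruction to defect size. If Type III and Type IV patients differ on these scores, two things follow in a trial of 24.

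- An uneven mix of types between the arms moves the unadjusted flap contrast in that particular trial, and an unpaired t test has no means of correcting for it.
- Even with an even mix, variation between types stays in the error term and lowers power.

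Both can be reduced by a baseline factor that costs one degree of freedom.

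**Working it through.** **The plan's own figure.** Cochran's formula with z = 1.96, P = 0.02 and e = 0.08 gives 1.96² × 0.02 × 0.98 / 0.08² = 3.8416 × 0.0196 / 0.0064 = 11.765, rounded up to 12 per group and 24 in total. The stated size reproduces. The formula contains no power, no effect size and no defect type, so it does not help with this question.

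**Inputs from the protocol.** 24 patients, 12 per arm, significance level 0.05.

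**Assumptions, because the protocol gives no figure.** 6, 8 or 12 of the 24 have one given type; the gap b between types is 0.5, 1.0 or 1.5 within-type SD; the true flap effect is 1 SD; the test is two-sided; scores are treated as continuous and normal (the plan itself compares means); allocation is validly random.

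**Chance of imbalance.** With K patients of one type, the number falling in one arm is hypergeometric: P(x) = C(K, x) × C(24−K, 12−x) / C(24, 12), where C(24, 12) = 2,704,156. The chance of a difference of 4 or more is 1 minus the chance of a difference of 0 or 2.

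- K = 12: 1 − (924² + 2 × 792²) / 2,704,156 = 1 − 0.780 = 22.0% (8:4 or worse).
- K = 8: 1 − (70 × 12,870 + 2 × 56 × 11,440) / 2,704,156 = 1 − 0.807 = 19.3% (6:2 or worse).
- K = 6: 1 − (20 × 48,620 + 2 × 15 × 43,758) / 2,704,156 = 1 − 0.845 = 15.5% (5:1 or worse).

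**Shift in the contrast.** A difference of 4 patients changes the share of that type by 4/12 between arms, so the raw mean difference moves by b/3: 0.17, 0.33 or 0.50 SD for b = 0.5, 1.0 or 1.5.

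**Precision.** With share s of one type, the variance seen by the t test is 1 + s(1−s)b². Effective sample size is 24 divided by this. The noncentrality is √6 / √(1 + s(1−s)b²) on 22 degrees of freedom unadjusted, and √6 on 21 degrees of freedom when stratified and adjusted. The noncentral t gives:

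| Gap b | Variance, s = 1/3 to 1/2 | Effective N of 24 | Unadjusted power |
|---|---|---|---|
| 0.5 | 1.056 to 1.063 | 22.7 to 22.6 | 62-63% |
| 1.0 | 1.222 to 1.250 | 19.6 to 19.2 | 56-55% |
| 1.5 | 1.500 to 1.563 | 16.0 to 15.4 | 48-47% |

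Stratified and adjusted power is 64.7% throughout. Simulation (100,000 trials per setting, 8 or 12 of 24 of one type) gives unadjusted power of 62%, 55-56% and 45-47%, and about 63% at every gap when the factor is added without stratifying.

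**False positives with no flap effect, by simulation.** Overall, the unadjusted test rejects in 4.9 to 5.1% of trials. Given a difference of 4 or more, it rejects in about 6.4%, 10% and 14-15% for b = 0.5, 1.0 and 1.5, against about 5% adjusted. The two results agree. For b = 1.0 and K = 12, the rates by imbalance are 2.8% (difference 0), 4.1% (2) and 10.1% (4 or more), and 0.317 × 0.028 + 0.463 × 0.041 + 0.220 × 0.101 = 0.050. The 2.8% also shows that stratifying without adjusting would leave the test conservative.

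**The case against.** The strongest reply is that much of this rests on silence. A condensed article commonly leaves stratification factors and covariates to the full protocol or analysis plan, and repeated measures ANOVA can carry a between-patient factor. This stands for allocation: one may say only that the article names no stratum, not that the trial has none. It carries less weight for the analysis, because the unpaired t test is a stated choice and cannot take a covariate.

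Second, the protocol never defines the two types, never says that scores differ between them, and gives no SD. The Background remark on defect size concerns the choice of reconstruction and not the outcome. This stands. The link is plausible but undocumented, and every power figure above depends on an assumed gap. At 0.5 SD, adjusting without stratifying gains almost nothing.

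Third, a reader might infer that pooling the types biases the trial or raises its false-positive rate above 5%. The documents do not support that. Valid randomisation keeps the overall rate at about 5% without adjustment; the inflation is conditional on an imbalance that has occurred. The allocation wording, which adds an alternating selection after the computer list, leaves it unclear whether allocation is random throughout. That is a separate matter, and these figures assume it away.

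Fourth, the defect results from the resection, which follows allocation, so the type actually produced cannot define a stratum and is not a clean baseline covariate. This stands and determines the form of the fix.

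**Conclusion.** The point holds as an improvement in efficiency and robustness for the four secondary scores. It is not a demonstration that the trial is biased. The chance of a difference of 4 or more patients of one type is about 16 to 22%, and such a difference moves the raw contrast by one third of the gap between types. Depending on that unknown gap, the power lost relative to adjustment alone runs from about one percentage point (0.5 SD) through 7 to 8 points (1.0 SD) to 16 to 18 points (1.5 SD). Stratification adds about two points beyond adjustment.

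These figures assume valid random allocation, a 1 SD flap effect and normal scores in place of 1 to 5 grades. They also take 24 randomised patients. The Materials and Methods section instead speaks of 24 assessed, "with 12 patients meeting the criteria for the study"; with 12 in all, chance imbalance would be worse. Nothing here was calculated for the primary complication outcomes, and no conclusion about them follows.

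**What to change.** Record for each patient, before allocation, the defect type planned from the clinical examination and the MRI that the Study procedure section already requires. Since eligible patients are randomised and eligibility turns on defect type, some such judgement must already be made.

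In the Statistical analysis section, specify for tongue shape, swallowing, speech and mobility a model with group, visit and planned defect type as factors, and take the flap comparison from it in place of the unpaired t test. Keep the planned type in the model even where the resection produces the other type, because the actual type is determined after allocation.

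If allocation has not started, also generate the computer list separately for planned Type III and planned Type IV. If it has started, the model term alone restores about 5% conditional error and about 63% power under the assumptions above.

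The cost is one degree of freedom, one recorded item and, if stratified, a second list. No further patients or examinations are needed.
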